## Abstract

**Background:**

Family risk factors, e.g. low socioeconomic status or parental mental health disorders, can affect children’s health and development. Thus, targeted preventive services for families with psychosocial burden are crucial. The German Early Childhood Intervention (ECI) program is a preventive approach that aims to strengthen parent’s resources by supportive services. However, research has revealed that only a proportion of the families considered to have substantial risk factors access the ECI program. To increase pediatricians’ skills in identifying risk factors, and to improve the cross-sectoral collaboration between relevant professionals and the referral of families to supportive services, the PATH-intervention (Pediatric Attention To Help) was developed. The PATH-intervention includes interprofessional quality circles and a one-day training program for the pediatricians. This study aims to evaluate this complex cross-sectoral care intervention for families with psychosocial burden.

**Methods:**

Using a prospective quasi-experimental, controlled (matched-pair), longitudinal mixed-method design, we will compare families under treatment of pediatricians trained in the PATH-intervention with families under treatment of a control group of pediatricians. Participating families are asked to complete online-surveys. As a primary outcome, we will examine the use of supportive services of the ECI by burdened families. Secondary outcomes are the proportion of correctly identified families with psychosocial burden by the pediatricians, as well as information provision and motivation of the families to use the supportive services. Additionally, the cost-effectiveness ratio will be investigated. In the process evaluation, we will qualitatively explore the acceptance of the PATH-intervention of all involved stakeholders and the treatment fidelity of the trained pediatricians.

**Discussion:**

This study will determine whether the PATH-intervention enables the pediatricians to identify and recommend supportive services to burdened families, as well as the families’ use of the supportive services of the ECI. Qualitative data will give insight into the acceptance of the intervention from the perspective of all stakeholders and the treatment fidelity. Results of this study could be the starting point for the broader implementation of the PATH-intervention as standard care.

**Trial registration:**

German Clinical Trials Register (DRKS): DRKS00023461 (3rd December 2020); WHO UTN: U1111- 260-6575.

**Supplementary Information:**

The online version contains supplementary material available at 10.1186/s12913-022-07787-9.

## Background

In the last two decades, increasing attention has been paid to risk factors affecting children’s health and development [1–3]. Risk factors include, among others, low socioeconomic status, parental mental health disorders (e.g. depression), parental adverse childhood experiences, unplanned pregnancy or early parenthood, domestic violence and substance abuse [1, 4, 5]. There is evidence that an accumulation of risk factors affects children’s wellbeing, health and developmental outcomes, and can also influence physical and mental health in later adult life [1, 6].

In Germany, a representative survey of families with small children (aged 0 to 3 years) revealed that 12.9% of the families reported four or more risk factors [5], indicating a high psychosocial burden on those families. Similar results were found in a representative survey among pediatricians: 13.8% of the families visiting a preventive medical check-up for their child were considered to have notable risk factors. More precisely, pediatricians rated these families as being under psychosocial stress, which could have a significant impact on the further development of the children involved. Frequently reported issues were being a single parent, low educational level, poverty, and parent exhaustion [7].

Given the negative consequences of risk factors on children’s development, targeted preventive services for families with psychosocial burden and children at risk are crucial. The German Early Childhood Intervention (ECI) program (“Frühe Hilfen”) represents a nationwide implemented preventive approach that aims to strengthen parent’s resources through supportive services. For example, these voluntary services comprise long-term home visiting services by healthcare professionals who have additional qualifications in psychosocial care (family midwifes or nurses), specific counseling services, or parent-child-groups. Such services can have benefits for the further development of children and, from a socioeconomic perspective, society as a whole [8, 9].

In order to overcome the “prevention dilemma”, which describes that especially families with particularly high needs do not use supportive services [10], improved cross-sectoral collaboration between professionals of health and social services is needed. In this context, pediatricians play an important role. Commonly, families with small children regularly visit pediatricians for medical check-ups – the so-called “U-Untersuchungen”. These medical check-ups for infants span from birth until the age of five (named U1 to U9). Over 95% of the families with small children make use of these preventive check-ups – throughout all social classes [11]. Thus, these check-ups provide a good opportunity to detect risk factors of families and to recommend regional supportive services.

However, research revealed that only one in every six families that are considered by a pediatrician to have substantial risk factors, actually access the ECI program [7]. One possible reason for this situation might be that the pediatricians frequently adopt a wait-and-see position. Furthermore, pediatricians and parents predominantly address psychosocial burden indirectly and rarely discuss them in depth [12]. Lastly, one in every five pediatricians find it difficult to identify psychosocial burden and risk factors during a medical check-up [7]. They also report a lack of time and inappropriate financial compensation for counseling.

To increase pediatricians’ skills to identify risk factors and their conversation skills to discuss psychosocial burden with families, as well as to improve the cross-sectoral collaboration between relevant professionals and the referral of families to the supportive services of the ECI, the National Center for Early Prevention (NZFH) developed the PATH-intervention (Pediatric Attention To Help) in cooperation with the Association of Statutory Health Insurance Physicians of the German state of Baden-Württemberg [13].

So far, no comprehensive evaluation of this complex healthcare intervention has been conducted. Considering the potential benefits of the ECI services on the further development of children, the overall objective of this study is to evaluate the PATH-intervention, which aims to facilitate a precise referral of families with small children (aged 0-3 years) and psychosocial burden to the supportive services of the ECI.

## Method

### Intervention

The PATH-intervention aims to promote cross-sectoral collaboration between pediatricians, child and youth welfare services (CHWS), and further agents of healthcare and psychosocial supportive services for burdened families with small children (aged 0-3 years). Its goal is a more frequent and targeted referral of families to the ECI system. The PATH-intervention comprises two central elements: interprofessional quality circles (IQCs) and a one-day training program for pediatricians.

Since 2010, the Association of Statutory Health Insurance Physicians of the German state of Baden-Wuerttemberg established stepwise-accredited interprofessional quality circles that include pediatricians as well as social workers and others (e.g. gynecologists, psychotherapists) from the CHWS and ECI services. Specially trained moderating tandems consisting of pediatricians and staff members from CHWS lead the IQCs [13]. The IQCs take place twice a year. The topics are case conferences on family burden. These case conferences target the planning of preventive measures to support the burdened family from an interprofessional perspective. Other issues of the IQCs are the discussion of developmental risks of children and becoming more familiar with supportive services in the respective regional area.

The one-day training program compiled by [name] and [name] ([name], [name]: Schulungsunterlagen zur Ausbildung der Moderatorentandems für IQZ sowie für die Instrumente der Fallfindung und des motivierenden Elterngesprächs, unpublished) aims to enhance the pediatricians’ skills to facilitate the family’s disclosure of sensitive information about the child’s care situation, the family’s burden and resources, to explore the family’s motivation of change and to refer them to the local organizations of the ECI, or directly to tailored supportive services. The training focusses on (1) specific aspects of the pediatrician’s interview style, such as questions about psychosocial issues and living conditions, supportive statements and encouragement of parental narration [14]; (2) principles of motivational interviewing (e.g. collaboration, evocation and autonomy supportive) [15]; (3) tailoring interventions to the family’s wish to change [16]; (4) dealing with indications of child maltreatment [17]; and (5) transferring the family to the local organizations of the ECI and supportive services [18]. In cases of uncertainty about the extent of the family’s psychosocial burden, they should use an interview guide to capture specific risk factors (e.g. parental depression, regulation disorders).

### Research aim and hypotheses

In order to evaluate the PATH-intervention, we compare families under treatment of trained pediatricians in the German state of Baden-Württemberg (IG) with those of a control group (CG; pediatricians not participating in the PATH-intervention) in the German state of Bavaria. More precisely, we put forward the following hypotheses: (1) Families with psychosocial burden who are under treatment of an IG-pediatrician use supportive services more often than burdened families treated by a CG-pediatrician (primary outcome). (2) As a precondition for successful referral to supportive services, we assume that pediatricians in the IG are better than their counterparts in the CG at (2a) identifying families with psychosocial burden, (2b) informing them about regional ECI services, and (2c) motivating them to use these services (proximal secondary outcomes). Thus, the proportion of families, who received information and were motivated, will be higher in the IG than in the CG. (3) From a socioeconomic point of view, the ratio between costs and effectiveness of the PATH-intervention will be positive (distal secondary outcome). (4) All involved stakeholders - the families with small children (0-3 years), pediatricians and members of the ECI network - appraise the PATH-intervention in a positive way (distal secondary outcome).

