One secondary distal outcome is the ratio between costs of the intervention and its effectiveness. In a first step, the total costs of the PATH-intervention will be calculated from the healthcare perspective. The following three aspects form part of the costs of the PATH-intervention: (1) the mandatory one-day-training program for the pediatricians, (2) the continuous participation in the IQCs (twice a year), and (3) reimbursement of certain aspects of the PATH intervention (e.g. identification of burdened families, information provision). All of the three aspects are associated with direct costs, which will be collected from the Association of Statutory Health Insurance Physicians of the German state of Baden-Wuerttemberg and outlined from the healthcare perspective. Both the one-day training program and the participation in IQCs are additionally associated with training credit points for the participating pediatricians, which will be monetarized using opportunity costs and outlined as an additional (societal) perspective. As part of a budget-impact analysis, health insurance claim data from the Statutory Health Insurance “AOK” Baden-Württemberg will be inspected in order to identify the number of individuals that might be applicable to the PATH-intervention in the case of a broader rollout of the program.

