#### Process evaluation

##### Cost-effectiveness analysis

The cost-effectiveness of the PATH-intervention will be analyzed by calculating incremental cost-effectiveness ratios (ICERs) for the following primary and secondary outcomes:Additional costs per use of supportive services by families with psychosocial burden.Additional costs per correctly identified family with psychosocial burden by the pediatrician.Additional costs per additional informing of an identified family by the pediatrician about regional supportive services and motivating them to use these services.

All ICERs will be determined separately from the healthcare and societal perspective and 95% confidence intervals will be calculated based on Fieller’s theorem [28].

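### Hypothesis 3 expects a positive cost-effectiveness ratio, but with PATH costs in the intervention group only, the sign merely repeats the direction of effect and cannot show value for money

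*Protocol article*

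**What the plan says.** The protocol article, under *Research aim and hypotheses*, lists as hypothesis 3, a distal secondary outcome viewed socioeconomically, that "the ratio between costs and effectiveness of the PATH-intervention will be positive". The same section describes the control group as "pediatricians not participating in the PATH-intervention".

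Under *Secondary outcomes*, the cost side is the cost of the programme itself: "the total costs of the PATH-intervention will be calculated from the healthcare perspective". The components are introduced by "The following three aspects form part of the costs of the PATH-intervention" and are:

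- "the mandatory one-day-training program for the pediatricians";
- continuing attendance at the interprofessional quality circles;
- "reimbursement of certain aspects of the PATH intervention".

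The societal view adds opportunity costs for the training credit points. Claims data from one insurer in Baden-Württemberg are used in a budget-impact analysis, to count the people to whom PATH might apply.

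Under *Cost-effectiveness analysis*, the ratios are ICERs: additional cost per use of services, per correctly identified family, and per family informed and motivated. "All ICERs will be determined separately from the healthcare and societal perspective", with 95% intervals by Fieller's theorem. The article gives no threshold, willingness-to-pay value or net-benefit rule.

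**The concern.** A hypothesis about cost-effectiveness should be able to come out differently for a cheap programme and an expensive one with the same effect. An ICER is a ratio of two differences. If the numerator can only be above zero, the sign of the ratio carries only what the denominator already says. Hypothesis 3 would then be met whenever hypothesis 1 (or 2a to 2c) points the right way, and the price would play no part.

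The *Discussion* says the results could form the basis for wider implementation as standard care. A reader who sees hypothesis 3 reported as confirmed could take it as separate economic support, although it would show only that more families in the intervention group used, or were guided to, services.

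**Working it through.** The plan states no figure for this hypothesis, so there is none to reproduce. The check is algebraic, followed by an illustration at the planned size.

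**1. Sign of the ratio.** Let dC be incremental cost and dE incremental effect, with ICER = dC / dE.

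- Intervention group: training + quality circles + reimbursement (+ opportunity cost in the societal view), each above zero.
- Control group: no participation, so PATH cost = 0.
- Hence dC > 0 in both perspectives, and sign(ICER) = sign(dE). For a given outcome, the healthcare and societal ICERs always share the same sign.

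**2. Indifference to price.** The article gives no cost per family. Assume dC between 10 and 10,000 EUR per burdened family (an assumption, for illustration only):

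| dE | ICER at dC = 10 EUR | ICER at dC = 10,000 EUR |
|---|---|---|
| 0.40 (planned: 50% − 10%) | 25 | 25,000 |
| 0.01 | 1,000 | 1,000,000 |
| 0.001 | 10,000 | 10,000,000 |
| −0.05 | −200 | −200,000 |

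Every row with dE > 0 meets the hypothesis, at either price. Only dE < 0 fails it.

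**3. How often the point ICER is positive.** Inputs from *Sample size considerations*: 800 families asked, 50% participate, 15% burdened, 30% drop out. Evaluable burdened families = 800 × 0.50 × 0.15 × 0.70 = 42, or 21 per arm. With independent binomial counts X (intervention) and Y (control), each out of 21, P(ICER > 0) = P(X > Y), and the ICER is undefined when X = Y:

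| True use, intervention vs control | P(ICER > 0) | P(undefined) |
|---|---|---|
| 10% vs 10% | 0.396 | 0.209 |
| 15% vs 10% | 0.601 | 0.168 |
| 20% vs 10% | 0.759 | 0.116 |
| 50% vs 10% | 0.998 | 0.001 |

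Check on the first row by symmetry: (1 − 0.209) / 2 = 0.396. Cost does not enter any of these probabilities.

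**4. The Fieller interval.** Treat dC as fixed and let (L, U) be the 95% interval for dE.

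- If L > 0, the set for the ICER is (dC/U, dC/L), wholly above zero.
- If L < 0 < U, the set is unbounded and includes negative values.
- If U < 0, it is wholly below zero.

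The interval therefore excludes non-positive values only when the interval for dE does. That is the question of hypothesis 1, or of 2a to 2c for the other ratios. Reading the criterion on the interval rather than on the point estimate makes it stricter, but still not economic.

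**The case against.** The strongest reply is that the article states an expectation, not a pass mark. Hypothesis 4 uses the same word to mean favourable, and hypothesis 3 may do so too. A willingness-to-pay range can properly sit in a fuller plan that is not shown. The planned analysis is estimation: ICERs for several outcomes from two perspectives, with intervals, plus a budget-impact analysis.

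Much of this stands. The absence of a threshold from an article is not the complaint. Nor does the favourable reading rescue the hypothesis: the planned ICERs and Fieller intervals contain no rule by which favourable value could be shown. On either reading the printed wording needs changing.

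Several stronger conclusions might be inferred, and the documents do not support them:

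- *That the article declares PATH successful on the sign of the ICER.* It does not. It lists a hypothesis, and it ties implementation to the study's results as a whole.
- *That the economic analysis is uninformative.* A cost per additional using family with its interval lets a reader tell 25 EUR from 25,000 EUR. Only the sign is empty.
- *That a cost-saving programme would fail, or a cheaper and worse one pass.* Both need dC < 0, which the listed costs exclude. The article says the three aspects are part of the costs, and Table 1 names claims data for this outcome. However, no saving entering the ratio is described, and no control-group cost source is named.
- *That hypothesis 3 is met half the time by chance, or can hardly fail.* At the planned size the point ICER is positive in about 40% of null trials. Judged on the interval, the figure is nominally about 2.5%, ignoring clustering.
- *That an unbounded Fieller set is an error.* It correctly reports that the ratio is undetermined.

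**Conclusion.** The point holds as a badly chosen criterion for one distal secondary hypothesis. On the costs listed, a positive ICER is equivalent to a higher effect in the intervention group, so hypothesis 3 duplicates the direction of hypotheses 1 and 2 and cannot show value for money. For the primary outcome at 21 families per arm, the point ICER is positive in about 40% of trials under 10% vs 10% (a further 21% undefined) and in about 99.8% under 50% vs 10%, at any price.

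The sign argument assumes that the listed components are the whole of dC and that the control group has no PATH cost. The probabilities assume independent families, 21 evaluable per arm and no covariate adjustment; clustering would change them but not the equivalence. The Fieller statement treats cost as fixed. The primary outcome, the data collection and the ICER estimates themselves are unaffected.

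**What to change.** Drop the sign as the criterion and choose one of two courses:

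- Restate hypothesis 3 as incremental net benefit above zero, λ × dE − dC > 0, over a stated range of willingness to pay λ per additional using family, shown as a probability across that range. This criterion responds to price: with dE = 0.40 and an assumed dC of 1,000 EUR it is met only if λ exceeds 1,000 / 0.40 = 2,500 EUR.
- Remove the hypothesis and report the cost-effectiveness results descriptively.

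In both cases, report incremental cost and incremental effect separately beside each ICER. In addition to the Fieller interval, give uncertainty that respects clustering, for example by resampling pediatricians. If savings are meant to enter the ratio, say so and name the source in both groups.

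The cost is a change of wording and slightly more analysis work, with no new data collection. The one real burden, under the first course, is that the sponsor must name a willingness-to-pay range; the documents give no value for it.

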### Study design and setting

This study is designed as a prospective quasi-experimental, controlled (matched-pair), longitudinal mixed-method trial [19]. It comprises a summative evaluation, as well as process evaluative study sections (Fig. 1). The summative evaluation is based on quantitative surveys. Participating families with small children (0-3 years) are asked to answer an online-survey at three measurement time-points: up to 7 days after a preventive medical check-up (U3-U7a) at the pediatrician (t1), follow-up at 6 weeks after the doctor’s visit (t2) and again 6 months later (t3). The pediatricians answer a questionnaire immediately after each medical check-up with a participating family. They will also answer a brief questionnaire on confounding factors (e.g. work experience) after the completion of the recruitment of families. Additionally, the evaluation is complemented by health economic analyses, including the analysis of health insurance data. As part of the process evaluation, we will conduct individual telephone interviews with participants of all stakeholder groups involved in the intervention – families, pediatricians and ECI network members. Another part of the qualitative process evaluation are video-assisted observations during the medical check-ups to examine treatment fidelity of the IG-pediatricians.

**Fig. 1 Fig1:**
[figure not shown]
Study design of the PATH study

### Participants and recruitment

Study participants comprise the three groups involved in the intervention process: pediatricians, families with small children (0-3 years), and ECI network members. For all groups, signed informed consent is required for participation in this study.

#### Pediatricians

Pediatricians of the IG have to have passed the intervention training or comparable trainings, and at least two IQCs in the past 2 years. The Association of Statutory Health Insurance Physicians of Baden-Württemberg supports the NZFH in finding eligible pediatricians for participation. Pediatricians of the CG are recruited in collaboration with the Professional Association of Pediatricians of the German state of Bavaria. The NZFH obtains informed consent from all pediatricians willing to participate. Based on a retrospective matched pair approach, CG-pediatricians are matched to IG-pediatricians by gender and regional characteristics of the doctor’s office (rural vs. urban, and socio-economic area). Thus, these potential confounding variables should be homogenously distributed in the two groups. All participating pediatricians get an expense allowance of 60€ per recruited family, and additionally 60€ for participating in the interview study section.

